### Blinding

Due to the nature of the intervention, the participants cannot be blinded to the allocation.

During the first 32 weeks of the study period, only participants assigned to the intervention condition will have access to the modules. Thus, the trial manager will not be blinded when receiving messages or phone calls with questions regarding the intervention. Each participant will have a unique Drupal ID number that is not known to the trial manager through the intervention period. When analyzing the data, the trial manager cannot see the participant’s names, but instead only their ID number. The trial manager will thus be blinded when analyzing the study. Only the main developer in the project will have access to all the information.

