#### Waiting list

The participants in the control condition will have access to the SOS trial website but not to the modules or the message system. They can access an “Acute Help” page where they can seek help information, and a “My Profile” page where they can read the Informed Consent Form, the participant information and change their login and contact details (these features are also available to the participants in the intervention condition). Once the 32 weeks have passed, the first module of the intervention will be accessible for the participants in the control condition.

All participants can seek help and treatment during the trial. In material and messages with information about the study, the participants are furthermore encouraged to contact The Lifeline or their general practitioner if they are not feeling well.

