Demographic data regarding age, sex, education level and relationship status will be collected through the Trimbos/IMTA questionnaire for Costs associated with Psychiatric Illness.

Information on deliberate self-harm episodes will be calculated using a self-report questionnaire and hospital records obtained from the Danish National Patient Register and the Psychiatric Central Research Register.

The participant will, after the intervention, be asked if they have experienced any negative effects related to the intervention and will be encouraged to give feedback; for instance, if they have not completed all six modules they will be asked why. Lastly, the participants will also be given the Internet Evaluation and Utility Questionnaire consisting of 15 questions regarding the usefulness, credibility and helpfulness of the intervention [22].

Data will be collected on how many times the participants log in to the website, how much time they spend on the intervention, how many modules they start and how many messages they send to the trial manager. The self-report questionnaires will be answered on the website. The SPIRIT figure (see Fig. 2) provides an overview of the measures used in the trial and their time points. See the Additional file 1 for the SPIRIT checklist.

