### Safety of subjects

Specific measures are taken to secure the safety of subjects during the study period. Firstly, participants will only be enrolled in the study after they provide their telephone number and the number of a contact person (e.g., a family member, a physician or a friend). If the trial manager suspects that a contact person’s telephone number is not valid, she will call the number to check. Secondly, the Beck Scale for Suicide Ideation will be administered every second week over the first 6 weeks to survey the severity of suicidal thoughts. If a participant in either the intervention or the control condition scores ≥27 on the scale, they will receive a telephone call from the trial manager. If the participant cannot be reached during three attempts over 3 days, the participant’s contact person will be contacted. This procedure is communicated to the participant during the enrollment phase. The same procedure will be carried out if a participant ceases to follow the intervention without notifying the trial manager by e-mail or telephone. Thirdly, the SOS trial website lists contact information to psychiatric hospitals and suicide preventive clinics in the event of a crisis. Fourthly, participants will via messages be encouraged to contact The Lifeline or their general practitioner if they are feeling unwell. Fifthly, participants can contact the trial manager by e-mail or telephone if they have questions or concerns. Additionally, a safety protocol has been developed for the study for cases of acute crisis where the trial manager is worried that a participant is in the process of planning a suicidal act. If this happens, the trial manager will, through the website, obtain access to the participant’s personal identifier number, and call the Danish alarm central. They can, with the participant’s personal identifier number and telephone number, track the person and request an ambulance or the police.

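### Hiding names behind ID numbers does not blind the trial manager to allocation at analysis, so the claim of a blinded analysis does not follow from the procedure described

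*Protocol article*

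**What the plan says.** The Blinding section of the protocol article treats conduct and analysis separately.

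- **Conduct.** It concedes that "the trial manager will not be blinded when receiving messages or phone calls with questions regarding the intervention", because during the first 32 weeks "only participants assigned to the intervention condition will have access to the modules".
- **Analysis.** It states that "Each participant will have a unique Drupal ID number that is not known to the trial manager through the intervention period", and then that "When analyzing the data, the trial manager cannot see the participant’s names, but instead only their ID number". From this it concludes: "The trial manager will thus be blinded when analyzing the study".

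The Waiting list section says that control participants "will have access to the SOS trial website but not to the modules or the message system". The Secondary outcome measures section lists usage data, including "how many modules they start and how many messages they send to the trial manager", as well as log-ins, time spent on the intervention, negative effects and a 15-item questionnaire evaluating the program. The Statistical methods section makes evaluation, usage and negative effects part of the planned analysis, and builds the imputation models separately by randomization group.

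**The concern.** Blinding an analyst means that the analyst cannot tell which arm a record, or a coded group, belongs to. A pseudonymous ID does something else: it stops the analyst from recognising a person. The article derives the first property from the second, and the step fails.

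The person concerned is also the one who answers messages and calls from the intervention arm, and so has a part in delivering the treatment being evaluated. Participants are not blinded and the main outcomes are self-reported, so masking at analysis is one of the few protections left to claim. If the claim is not met, two things are at stake:

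- Readers of the results would be told that the analysis was blinded when the procedure described does not make it so.
- Choices left open in the analysis could be made by someone who knows the arms.

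**Working it through.** No formula applies to the claim itself. The check sets the relevant sections side by side.

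**Step 1: what the stated measure hides.** The Blinding section gives two facts: the ID is unknown to the manager through the intervention period, and only the ID is shown at analysis. Together they make it hard to link a remembered person to a row of data. Neither concerns the group variable. No coded label, withheld variable or separate analyst is mentioned.

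**Step 2: which planned variables reveal the arm before week 32.**

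| Variable (Secondary outcome measures) | Possible in the control arm before week 32? | Reveals the arm? |
|---|---|---|
| Log-ins to the website | Yes: controls have website access and answer questionnaires there | No, not alone |
| Modules started | No | Yes, if any |
| Messages to the trial manager | No | Yes, if any |
| Time on the intervention | No | Yes, if above zero |
| Negative effects of the intervention, program evaluation | No: both presuppose having had the program | Yes, if answered |

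After week 32 controls may start the program and answer post-intervention questionnaires, so the table holds for the comparison period only.

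**Step 3: how far one such variable reaches.** The trial has 219 + 219 = 438 participants. A record with a module start or a message before week 32 must be one of the 219 intervention records. If the group variable is coded A/B and sits beside such a field, one record of this kind identifies the code and so the arm of all 438. If no group variable is shown, only records with program activity are identified, somewhere between 0 and 219. As an illustration, the article reports that 21% of participants in the Dutch trial completed all six modules. If the same held here, 0.21 × 219 ≈ 46 participants would be identifiable as completers alone, and anyone who merely started a module would add to that.

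**Step 4: does the analyst need the group variable?** Yes. The comparisons need it, and imputation is done separately for each randomization group. A label must be present, and the article does not say that it is masked.

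**Step 5: where discretion remains.**

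- *Secondary outcomes other than depression and the long-term effect on suicidal thoughts.* These use ANCOVA with multiple imputation. The predictors of missingness and the auxiliary variables are to be identified outcome by outcome.
- *Primary outcome.* The model is a linear mixed model fitted by maximum likelihood with an unstructured covariance matrix, so the imputation choices do not touch it. The contrast, however, is stated in two ways. The Design section gives superiority at 6 weeks. Table 1 gives a time × group interaction over weeks 2, 4 and 6. These need not be the same test. If time is categorical with the four occasions named in Statistical methods (baseline, 2, 4 and 6 weeks), the interaction has (4 − 1) × (2 − 1) = 3 degrees of freedom, against 1 for the 6-week difference.

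**The case against.** The strongest reply is that coding of arms, data release and the order of unblinding usually belong in the analysis plan or full protocol, which are not shown, so a condensed article cannot be faulted for omitting them. That is right as far as it goes. The point here is not the omission. The article states a conclusion and gives its reason, and the reason does not support it.

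Other parts of the reply stand and limit the point:

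- **A reader might infer that every record is unmasked on sight.** That assumes a single file holding both usage and outcome data. The article describes no such file, and it lists usage and evaluation last, as descriptive work. What can be said is that no separation is described.
- **A reader might infer that any log-in record unmasks.** It does not, because both arms use the website.
- **A reader might infer that the safety calls carry arm and outcome into the analysis.** Participants with a score of 27 or more are told that "they will receive a telephone call from the trial manager", but this applies in both arms and does not itself show allocation. The ID safeguard limits linking a remembered call to a record.
- **A reader might see a contradiction with the statement that only the main developer can access all information.** The manager's access for safety is to particular items, and the personal identifier is obtained only in an acute crisis. That is compatible with the developer alone holding the full set.
- **A reader might add the choice of a fallback covariance structure to the open decisions.** The article mentions no fallback.

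**Conclusion.** The concern holds in a limited form. The sentence claiming a blinded analysis is not supported by the procedure given for it: IDs mask identity, while several planned variables reveal allocation within the 32-week comparison and nothing described keeps them from the analyst.

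The size of any bias cannot be derived from the article. The exposure lies mainly in the imputation choices for secondary outcomes and in the choice between the two stated primary contrasts. A reader might go further and infer that the primary result is biased. The documents do not support that: the outcome is self-reported, the model is largely fixed, and nothing says that the manager alone makes the analytic decisions.

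The conclusion assumes that usage and evaluation variables are available to the manager when the comparisons are run. If an unseen plan already separates them and codes the arms, the procedure is sound and only the article's reasoning needs correction. The matter should be settled before analysis, since the claim will otherwise be carried into the results report.

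**What to change.** Either make the claim true or withdraw it.

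1. **Make it true.** Have the main developer, who already holds all the data, export the outcome data with arms coded A/B and without usage, message, negative-effect and program-evaluation variables. Name the single primary contrast beforehand. Run and lock the primary and key secondary analyses, including the imputation models, on that file. Only then break the code and merge the withheld variables for the usage and evaluation analyses. State this sequence in the Blinding section in place of the present reasoning.
2. **Withdraw it.** Delete the sentence and state that the analyst is not blinded to allocation.

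The first option costs one staged export and a slightly later start to the usage analyses, with no extra staff. The second costs only the wording, but gives up the protection.

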### Strategies to improve adherence

Adherence in Internet-based therapies is often low; only 21% of the participants completed all six modules in the Dutch trial [7, 23, 24]. Three strategies will be applied to improve adherence: first, the trial manager will inform the participants over the telephone what it implies to participate in the study before they sign the Informed Consent Form. Second, the participants are encouraged to send messages to the trial manager if they have any questions. Third, participants will, through text messages, receive reminders with information when a new module is open and when they need to answer a new set of self-report questionnaires.

In addition, a successful administration of the self-report questionnaires at 6 weeks and 32 weeks will be rewarded with four cinema tickets. The participants assigned to the control condition will, in addition, receive a cinema ticket when they, after 32 weeks of waiting-list status, commence the intervention and answer the post-intervention questionnaires.

### Safety of subjects

Specific measures are taken to secure the safety of subjects during the study period. Firstly, participants will only be enrolled in the study after they provide their telephone number and the number of a contact person (e.g., a family member, a physician or a friend). If the trial manager suspects that a contact person’s telephone number is not valid, she will call the number to check. Secondly, the Beck Scale for Suicide Ideation will be administered every second week over the first 6 weeks to survey the severity of suicidal thoughts. If a participant in either the intervention or the control condition scores ≥27 on the scale, they will receive a telephone call from the trial manager. If the participant cannot be reached during three attempts over 3 days, the participant’s contact person will be contacted. This procedure is communicated to the participant during the enrollment phase. The same procedure will be carried out if a participant ceases to follow the intervention without notifying the trial manager by e-mail or telephone. Thirdly, the SOS trial website lists contact information to psychiatric hospitals and suicide preventive clinics in the event of a crisis. Fourthly, participants will via messages be encouraged to contact The Lifeline or their general practitioner if they are feeling unwell. Fifthly, participants can contact the trial manager by e-mail or telephone if they have questions or concerns. Additionally, a safety protocol has been developed for the study for cases of acute crisis where the trial manager is worried that a participant is in the process of planning a suicidal act. If this happens, the trial manager will, through the website, obtain access to the participant’s personal identifier number, and call the Danish alarm central. They can, with the participant’s personal identifier number and telephone number, track the person and request an ambulance or the police.

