### Intervention

Participants assigned the intervention condition will receive a Danish translation of the Dutch intervention, “Living under control” [7].

The intervention and its theoretical background has been described in detail elsewhere [9–11]. It consists of six modules that each takes a week to complete [7]. Every module starts with a theoretical section followed by one compulsory exercise, several optional exercises and a Frequently Asked Questions section. The participants are encouraged to use a minimum of 15 min twice a day to carry out the exercises and they can, through a message system on the website, write to the trial manager if they have any questions or concerns. It is up to each participant if they want to receive any help from the trial manager or just want to go through the intervention without any guidance.

The first of the six modules aims to help the participants to gain more control over their suicidal thoughts. Participants will be encouraged to schedule specific “worry times” during the day, e.g., 8 a.m. and 8 p.m., where they force themselves to think about all the things that upset them. The participants will be asked to perform this exercise every day for the 6 weeks that the intervention lasts. They will also be asked to tally every time they have a suicide-related thought as a means to be more conscious about their thoughts and how often they think about suicide.

In the second module, the participants will develop a crisis plan and practice how to tolerate intense emotions. The third module focuses on how participants can influence their feelings by being aware of negative thoughts. In the fourth module, the participants will be introduced to negative thinking habits and how these might influence thoughts and feelings. In the fifth module, the participants will be offered exercises aimed to help them reformulate negative thoughts. The last module focuses on the future and will help the participant make a relapse prevention plan.

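### As worded, neither safety-call trigger covers a waiting-list participant who silently stops returning the Beck scale at weeks 2, 4 or 6

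*Protocol article*

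**What the plan says.** All of the following is in the protocol article.

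- **Monitoring tool (Safety of subjects).** "the Beck Scale for Suicide Ideation will be administered every second week over the first 6 weeks to survey the severity of suicidal thoughts".
- **Trigger 1 (Safety of subjects).** "If a participant in either the intervention or the control condition scores ≥27 on the scale, they will receive a telephone call". After three failed attempts over 3 days, the contact person is approached. On telling participants about this: "This procedure is communicated to the participant during the enrollment phase".
- **Trigger 2 (Safety of subjects).** "The same procedure will be carried out if a participant ceases to follow the intervention without notifying the trial manager by e-mail or telephone".
- **What the intervention is (Intervention).** "It consists of six modules that each takes a week to complete".
- **When controls receive it (Waiting list).** "Once the 32 weeks have passed, the first module of the intervention will be accessible for the participants in the control condition". The Blinding section agrees: "During the first 32 weeks of the study period, only participants assigned to the intervention condition will have access to the modules".
- **Reminders (Strategies to improve adherence).** Text messages tell participants when questionnaires are due. No step is stated if a reminder goes unanswered.
- **Separate safety document (Safety of subjects).** "a safety protocol has been developed for the study for cases of acute crisis". It is described for situations in which the trial manager is already worried that a suicidal act is being planned.

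**The concern.** The article accepts that unexplained disengagement deserves a call, because it states a rule for it. It then ties that rule to following a programme that only one arm has during the monitored six weeks. The other trigger depends on a score, and a person who has stopped answering provides none.

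The population makes this matter. Eligibility sets a lower Beck cutoff but no upper one, and the Discussion says that people with severe suicidal thoughts are included. The two-weekly Beck scale is the stated way of watching severity. For a waiting-list participant it is the only stated check during these weeks that does not rely on the participant asking for help. A missing scale may mean deterioration or merely lost interest. Without a call the trial manager cannot tell which.

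**Working it through.** The plan gives no figure on this point, so the main check sets each trigger against each kind of silence in weeks 2 to 6, taking the text as worded.

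| Participant, no notice given | Trigger 1 (returned score ≥27) | Trigger 2 (stops following the intervention) | Call stated? |
|---|---|---|---|
| Either arm, returns a scale scoring ≥27 | Met | Not needed | Yes |
| Intervention arm, stops using the modules | Only if a scale is returned | Met | Yes |
| Intervention arm, uses the modules but skips the scale | No score | Not met | No |
| Control, skips the scale | No score | Cannot be met before week 32 | No |

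1. Trigger 1 names both conditions but needs a completed questionnaire, and the questionnaires are filled in by the participant on the website (Secondary outcome measures).
2. Trigger 2 names no condition. Its content is the six-module programme, which controls cannot open until after week 32.
3. The remaining measures open to controls are text reminders, the Acute Help page, encouragement to contact The Lifeline or a general practitioner, and the option to contact the trial manager. None is a call set off by non-response.
4. The acute-crisis protocol, as described, starts from a worry that the trial manager already has. Silence alone gives no such signal.

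**Scale.** The documents give no count of participants who fall silent without notice. Two figures in the Sample size section can serve only as illustrations, assuming equal loss in the two arms (438 / 2 = 219 controls):

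- Dutch trial, about 10% not completing all post-test questionnaires: 0.10 × 219 = 21.9, about 22 controls.
- Planned dropout allowance of 20%: 0.20 × 219 = 43.8, about 44 controls.

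Neither measures silence. Both can include people who withdrew with notice, who returned the scale at weeks 2 and 4, or who missed only other questionnaires. They also say nothing about someone who missed an early scale but answered at week 6.

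**Call burden.** The procedure allows three attempts, so the ceiling is 3 per missed scale and 3 × 3 = 9 per person if all three scales are missed. If 22 to 44 controls each missed one scale and every attempt failed, that would be 3 × 22 = 66 to 3 × 44 = 132 attempts. A call answered at the first attempt counts once, so the real number would be lower for the same number of silent controls. Calls to intervention participants who skip the scale would be additional.

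**Timing.** With an example grace period of 7 days plus 3 days of attempts, the attempts end by day 10, before the next scale 14 days on. The contact-person step follows those attempts. This spacing argument applies only to the week 2 and week 4 scales, because the next assessment after week 6 is at week 32.

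**The case against.** The strongest reply is that trigger 2 was meant for everyone. Its subject is any participant, it directly follows a rule covering both conditions, and notice is by e-mail or telephone, channels open to all. The message system, by contrast, belongs to the intervention arm. Read as stopping participation without telling the trial team, it would cover controls. This stands as a plausible account of intent. It does not remove the problem for someone following the text, which names the intervention, and the same rewording settles the matter either way.

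A second reply is that a journal article condenses, and that the handling of missed questionnaires belongs in the full protocol or the safety protocol. This limits the point to what the article states. But the article does not simply leave disengagement out: it gives a rule whose wording fits one arm. The safety protocol is described only for acute crisis, so it cannot be assumed to hold the missing rule.

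Third, controls are not abandoned. Besides the measures already listed, the trial manager speaks with each participant before consent, a contact person is compulsory, and controls may seek any treatment. All of this stands. A reader might infer that controls have no safety net, or that silent controls will in fact go uncalled; the documents support neither reading.

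Last, following up non-response has a price: a relative, friend or physician may be contacted over a missed questionnaire, and controls get more staff contact before the primary endpoint. These are real but small, since the sponsor already accepts the same escalation for scores of 27 or more in both arms and for disengagement in the intervention arm.

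**Conclusion.** The point holds as a defect of wording in a stated safety rule. Before week 32 the disengagement trigger, read literally, cannot reach waiting-list participants, and the score trigger cannot reach anyone who does not return the scale. A missed scale by itself prompts no stated call in either arm. The arms differ in that an intervention participant who also drops the modules is covered, while a silent control has no equivalent.

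The number affected is unknown, and the illustrative 22 to 44 controls should not be read as an estimate. The conclusion rests on the literal meaning of the second trigger and on the article alone; the safety protocol was not available and could contain a non-response rule. Nothing here shows an error in the sample size, the analysis or the primary estimate. It is a cheap improvement worth making.

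**What to change.** Reword the second trigger along these lines: *The same steps apply when a participant in either condition stops using the modules they have been given, or leaves a scheduled Beck scale unreturned beyond a set grace period after its reminder, and has not told the trial manager by telephone or e-mail.*

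Explain this at enrolment, as is already done for the score-based call. The grace period is for the sponsor to choose. Seven days is one example; it should be long enough that late responders are not escalated to the contact person. If the safety protocol already contains such a rule, a sentence in the article saying so would be enough.

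The change uses the existing caller, telephone numbers and escalation steps, and adds no questionnaire. Its costs are the extra calls (at most three attempts per missed scale), some intrusion through the contact person, and slightly more staff contact with controls before the week-6 measurement.
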